**Fig. 1 Fig1:**
[figure not shown]
Study design

**Table 2 Tab2:**
[figure not shown]
Schedule of enrolment, interventions, and assessments as recommended by the Standard Protocol Items: Recommendations for Interventional Trials (SPIRIT) statement [41]

*Optional CBT-I and T2 after waiting list not shown here in the interest of readability

The effect size for the CBT-I treatment in our feasibility study [29] (*n* = 22) was *d* = 0.76, corresponding to *f* = 0.38. The correlation among the repeated measures reached a value of *r* = .67. Setting the *α*-error probability at .05, *β*-error probability at .20, the number of groups at 3, and the number of measurements at 2, we calculated a required sample size of *N* = 15 using the ANOVA repeated measures, within-between interaction setting of the G*Power software [42]. If we adjust the effect size to a more conservative *f* = 0.25, the required sample size is *N* = 30. Consistent with this magnitude, Bortz and Schuster [43] recommend a sample size of at least *N* = 19 for large effect sizes, high power values, and low α-error probabilities. Expecting a maximum dropout rate of 50%, as observed in the feasibility study, we aim to allocate 60 participants and evaluate at least 30 participants (10 per group). We will make an effort to obtain assessments for participants who drop out of the study to facilitate carrying out intention-to-treat analyses.

Company physicians and social counseling services at collaborating companies will inform their workforce about the trial and screen those interested for eligibility. They will use flyers and posters to reach as many potential participants as possible, for example on company health days. They will also be the ones to obtain informed consent before granting access to our anonymous online platform. No personal information about potential or enrolled trial participants will be shared with the investigators. Vice versa, investigators will not share personal information with the company physicians and social counseling services. Exceptions to this rule are groups of at least ten participants, where sample characteristics, such as the average rate of improvement, may be communicated to the enrolling services in collaborating companies. No such data will be shared if inferences to individual cases are possible at any level or if any subsample of interest is smaller than ten.

Group assignment takes place immediately after receiving T0 measurements. The CBT-I professionals will assign their respective participants to the intervention and the waiting group in a 1:1 ratio using an Excel sheet, where every anonymous, randomly assigned access code has been randomly assigned a value of 0 or 1, corresponding to the waiting list and the intervention group respectively. Those responsible for data evaluation will be blinded regarding group assignments. Participants and providers will be aware of the assignment.

Participants will enter their baseline (T0) and outcome (T1) data described under Outcomes, as well as their sleep diaries through our online platform and transmit it to the Institute’s servers. We will contact participants that dropped out or otherwise failed to transmit four sleep diaries for T1 measurements.

Data will be exported from our servers and entered into SPSS [44] via the program’s syntax function. The raw data will remain on the servers for storage security. We will check the data for errors resulting in outliers or missing values. Missing values will not be replaced. Dropouts will be analyzed separately Group comparisons and superiority tests will be computed in SPSS using repeated measures ANOVA.

A data monitoring committee will not be needed, as the CBT-I professionals are not blinded during the trial and can react to any adverse events. The sleep restriction element of the CBT-I intervention is the only part of the trial where adverse events are expected to occur based on experiences from outpatient treatment with the same contents. If a participant reports issues in the form of a critical drop in total sleep time (< 4h for 7 nights or more) with this part of the treatment, CBT-I professionals are instructed to try to use a less strict approach. If this is still not tolerated well enough, we will stop sleep restriction and proceed with the rest of the contents. This should result in a quick recovery. Reports of adverse events will be collected alongside any other solicited or spontaneously reported feedback from participants. Interim analyses, trial conduct audits, and stopping guidelines are not intended at this point.

The study was approved by the ethics committee of the Lutheran University of Applied Sciences Nuremberg, Germany, under the trial ID am/sot. Changes to the protocol will be communicated to the sponsors, trials registry, and ethics committee within 6 months of their implementation.

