**Methods:**

Collaborating companies will offer our anonymous online intervention to their shift-working employees. Company physicians and counseling services will screen those interested for inclusion and exclusion criteria. Participants will receive access to our online service, where they will complete psychometric assessment and receive random assignment to either the intervention group or the waiting-list control group. Participants and providers will be aware of the group assignment. We aim to allocate at least *N* = 60 participants to the trial. The intervention consists of psychoeducation, sleep restriction, stimulus control, relaxation techniques, and individual feedback delivered via four e-mail contacts. During the intervention, as well as during the waiting period, participants will fill out weekly sleep diaries. Immediately after completion of the program, the post-intervention assessment takes place. Participants in the control group will be able to participate in the program after all study assessments. To recruit an additional sample, collaborating outpatient sleep clinics will provide six sessions of standard face-to-face CBT-I to an ad hoc sample of shift working patients. We expect both the online and the face-to-face CBT-I interventions to have beneficial effects compared to the control group on the following primary outcomes: self-reported symptoms of depression and insomnia, sleep quality, and daytime sleepiness.

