The standard treatment of sleep disorders not related to shift work is cognitive behavioral therapy for insomnia (CBT-I) [20, 21], which has consistently shown sustained moderate to large positive effects [22]. CBT-I has also been successfully applied in shift workers in two published studies [23, 24], where Järnefelt and colleagues have shown the potential for group delivered CBT-I interventions in participants who worked irregular hours and suffered from insomnia or SWSD. However, we argue that many shift workers might not be able to participate in regularly scheduled group or even one-on-one meetings due to their working hours. For the treatment of shift workers, we thus argue for a transfer of CBT-I contents from synchronous face-to-face to asynchronous online modes of communication, which do not rely on simultaneous presence of provider and recipient [25]. Multiple studies have shown the transfer of CBT-I contents to online settings to be feasible and effective in reducing insomnia symptoms, both in non-shift workers [26–28] and shift workers [29]. Improvements in sleep tracking and dropout rate management, as well as more validation studies and expanded public access, are needed [30, 31].

Our group conducted a non-randomized feasibility and non-inferiority trial on the effects of an online CBT-I intervention (*n* = 22) compared to a face-to-face setting (*n* = 20) [29]. We were able to show significant improvements regarding symptoms of insomnia and depression in both settings. Contents of the program are rooted in the CBT-I literature [32, 33] and have largely remained the same for this study. Based on the findings in the feasibility study, we adjusted the online platform and the study design in order to reduce the dropout rate and to increase the validity and transferability of the results. We will now begin to evaluate the efficacy of the online CBT-I intervention in a randomized controlled trial. In this manuscript, we present a description of the updated study protocol.

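### The f = 0.25 behind N = 30 assumes a larger effect than the pilot's d = 0.76; on that d, 10 evaluated per group gives about 51 to 52% power, not 80%

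*Protocol article*

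**What the plan says.** The sample-size paragraph in the protocol article's Methods (after Table 2) works in three steps.

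- It takes an effect from the group's own pilot: "The effect size for the CBT-I treatment in our feasibility study [29] (*n* = 22"), which "was *d* = 0.76, corresponding to *f* = 0.38". It adds: "The correlation among the repeated measures reached a value of *r* = .67". With α = .05, β = .20, three groups and two measurements, G*Power's repeated-measures within-between interaction returns N = 15.
- It then lowers the effect: "If we adjust the effect size to a more conservative *f* = 0.25, the required sample size is *N* = 30". This is the figure that is adopted.
- Allowing for at most 50% dropout, it concludes: "we aim to allocate 60 participants and evaluate at least 30 participants (10 per group").

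The Introduction describes the pilot as a non-randomised study of the "effects of an online CBT-I intervention (*n* = 22) compared to a face-to-face setting (*n* = 20"). No untreated group is mentioned. In the present trial only online versus waiting list is randomised. The abstract says "We aim to allocate at least *N* = 60 participants to the trial" and later describes the face-to-face patients as recruited in addition.

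**The concern.** An f of d/2 describes two group means compared once. A group-by-time interaction uses a different f: the standard deviation of the interaction cell effects divided by the within-cell SD. For the same difference in change, that f is about half as large. If d/2 is entered there, the required N comes out too small. Stepping down to 0.25 looks cautious only because the starting value of 0.38 was too high.

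The β of .20 is the justification given for the trial's size. If power is nearer one half, a null result would say little even if the pilot effect were fully real, and a reader of the protocol would not know this.

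**Working it through.** **Inputs, all from the sample-size paragraph:** d = 0.76, r = .67, α = .05, target power 80%, k = 3 groups, m = 2 measurements, 30 evaluated (10 per group).

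**1. Reproduce the plan's figures.** G*Power's default for this test uses a noncentral F with λ = f²·N·m/(1 − r), df1 = (k − 1)(m − 1) and df2 = (N − k)(m − 1).

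- f = 0.38, N = 15: λ = 0.1444 × 30/0.33 = 13.13, power 0.820.
- f = 0.25, N = 30: λ = 0.0625 × 60/0.33 = 11.36, power 0.821.
- Dropout: 30/(1 − 0.5) = 60.

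All three match. The other effect-size conventions (as in Cohen, as in SPSS) give N of 72 to 75 at f = 0.38 and 159 to 162 at f = 0.25, so the default was used. The computation is right for its inputs; the question is the f.

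**2. Interaction f for a difference in change of D SD.**

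- Two groups, changes D and 0: the interaction effects are ±D/4 in all four cells, so f = D/4. With D = 0.76, f = 0.19.
- Three groups, changes D, D and 0: the cell effects are ±D/6, ±D/6 and ±D/3. Their mean square is (1/36 + 1/36 + 4/36)/3 × D² = D²/18, so f = D/√18. With D = 0.76, f = 0.179.

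**3. What the plan's f values assume.**

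- f = 0.25: D = 4 × 0.25 = 1.00 (two groups) or 0.25 × √18 = 1.06 (three groups).
- f = 0.38: D = 1.52 or 1.61.

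Both exceed 0.76.

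**4. Power at 10 evaluated per group with D = 0.76.**

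- Three-group interaction, N = 30, f = 0.179: λ = 0.5776/18 × 60/0.33 = 5.83, power 0.522.
- Randomised pair, 10 versus 10, f = 0.19: λ = 0.0361 × 40/0.33 = 4.38, power 0.508. This equals a t test on change scores with SD of change √(2 × 0.33) = 0.812. A simulation gave 0.507.
- Taking f = 0.25 at face value, the randomised pair has 74% (D = 1.00) to 79% (D = 1.06).

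**5. Sensitivity of the randomised comparison at 10 versus 10.**

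- Waiting list improves by 0.1, 0.2 or 0.3 SD: 41%, 31% or 22%.
- d standardised by the SD of change instead of the raw-score SD: 36%.
- r from .5 to .8: 36% to 72%.

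**6. Size needed (D = 0.76, r = .67, no control change).**

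- Randomised pair: 51% at 10 per arm, 70% at 15, 82% at 20; 80% is first reached at 19 per arm (38 in two arms).
- Three-group interaction: 54 in total with equal groups, against the 30 stated.

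**The case against.** Several stronger readings are tempting, and the protocol does not support them.

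- **That the halved d set the trial's size.** It did not. f = 0.38 gave N = 15, which was not adopted; 10 per group comes from f = 0.25. The fault that matters is that 0.25 is presented as cautious when it exceeds what d = 0.76 implies.
- **That d is a pre-post change.** A reader may infer this, because n = 22 is the online arm alone and no untreated group is described. The protocol does not say so, and gives neither contrast nor standardiser. The conversion problem does not depend on it: any 0.76 SD difference in change is f = 0.19 with two groups. A pre-post origin would make 0.76 optimistic, since change on the waiting list would have to be subtracted.
- **That 51% is the trial's power.** It is one scenario, and step 5 shows how far it moves.
- **That only 10 per group will be evaluated.** The 50% is a stated maximum, 30 is a minimum, and the investigators plan to seek T1 data from dropouts. With 20 evaluated per arm, power would be 82%. A calculation that treats 50% as the expected loss would overstate the problem.
- **That testing three groups is itself a mistake.** The hypotheses cover both CBT-I formats against control, so a three-group interaction can be defended. It does not rescue the claim: its own power at N = 30 is 52%.
- **That 60 people are randomised.** The abstract says 60 are allocated to the trial, not that 60 are randomised. The sample-size paragraph spreads the 60 over three groups, which with equal groups means 40 randomised. The two places need reconciling; neither settles it.

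What stands is the wrong f for the chosen test, and a power claim at N = 30 that does not follow from the pilot effect.

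**Conclusion.** The concern holds as an error in the effect-size input, not in the arithmetic. On the protocol's own d, r and α, 30 evaluated participants at 10 per group give about 52% power for the three-group interaction and 51% for the randomised online versus waiting-list comparison, where β = .20 implies 80%. These figures assume that d is in raw-score SD units, that the waiting list does not change and, for the three-group figure, that both CBT-I groups change by 0.76 SD. In none of the single-assumption variations examined does the randomised comparison reach 80% at 10 per arm; the highest is 72%, at r = .8. A difference in change of about 1.08 SD would be needed.

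**What to change.** Rewrite the sample-size paragraph.

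- Define d = 0.76: which outcome, which contrast and which standardiser.
- Replace the d/2 conversion with the interaction f (0.19 for two groups; 0.18 for three groups changing by d, d and 0).
- Remove the description of f = 0.25 as conservative, and the claims that N = 15 or N = 30 gives 80% power.
- State power conditionally for both tests. For the randomised pair: about 51%, 70% and 82% at 10, 15 and 20 evaluated per arm, with 19 per arm needed for 80%. For the three-group interaction: about 52% at 30 in total, with 54 needed. Give the assumptions, and the values under some control improvement, under the other standardiser and under other r.
- Reconcile the paragraph with the abstract on whether the 60 include the face-to-face group, and state the number randomised.

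The cost is rewording and a less favourable stated power; the correction itself needs no added enrolment. If the sponsor decides that the 60 are all randomised with face-to-face patients on top, that could mean about 20 more participants than the three-group reading. At 50% dropout it would leave 15 per arm, about 70% power, so that choice alone would not restore 80%.

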After registration, T0 measurements and randomized allocation, participants in both of the online groups will receive access to the first weekly sleep diary along with instructions on how to proceed. Every time participants in the online intervention group complete a week of diary entries, they will receive the next e-mail with individual feedback and further CBT-I contents. In the face-to-face intervention, participants will fill out sleep diaries between sessions. We will encourage participants to leave as few nights undocumented as possible; however, breaks in the sleep protocols will be permitted. Following our experience from the feasibility study, we expect that participants complete the program within 6 to 12 weeks. We will consider an intervention complete after a participant has received all CBT-I contents and filled out at least 4 weeks of sleep diaries.

T0 will include screening questions for sleep issues such as periodic limb movement disorder, sleep apnea, and sleepwalking, as well as questions regarding concurrent and previous treatments. Changes in medication will be reported in the sleep diaries. We will not exclude participants from the trial based on these questions; however, we might recommend alternative courses of treatment and we will control for relevant changes in treatment or medication during the trial when analyzing the data.

Outcome measures of the study will include data from at least four sleep diaries (total sleep time and time in bed for each night, average sleep efficiency across seven consecutive nights) as well as psychometric self-report scales at T0 and T1. The BDI-II is a 21-item self-report measure for depressive symptoms [35]. The RIS is a 10-item self-report questionnaire for cognitive, emotional, and behavioral aspects of psychophysiological insomnia [36]. The ESS is an 8-item self-report scale for daytime sleepiness [37]. In addition, T0 will include the 15-item self-report Morningness-Eveningness-Stability-Scale improved (MESSi) [39], from which the individual chronotype will be calculated, as well as three screening questions for sleep apnea, snoring, and periodic limb movement disorder. This will be used to guide the CBT-I treatment and explore potential differences in treatment response [40].

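### The analysis rule, read plainly, takes dropouts out of the randomised online versus waiting-list comparison and conflicts with the intention-to-treat aim for which their T1 data are collected

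*Protocol article*

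**What the plan says.** All the relevant text is in the Methods of the protocol article.

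- **Analysis paragraph.** On missing data: "Missing values will not be replaced. Dropouts will be analyzed separately". On the test: "Group comparisons and superiority tests will be computed in SPSS using repeated measures ANOVA".
- **Sample-size paragraph (after Table 2).** "Expecting a maximum dropout rate of 50%, as observed in the feasibility study", and from this "we aim to allocate 60 participants and evaluate at least 30 participants (10 per group"). The next sentence reads: "We will make an effort to obtain assessments for participants who drop out of the study to facilitate carrying out intention-to-treat analyses".
- **Data collection paragraph.** "We will contact participants that dropped out or otherwise failed to transmit four sleep diaries for T1 measurements".
- **Definition of completion.** "We will consider an intervention complete after a participant has received all CBT-I contents and filled out at least 4 weeks of sleep diaries".

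Only the online and waiting-list groups are randomised (1:1). The face-to-face group is a non-randomised sample. Nothing in the article says that a T1 obtained from a dropout enters the superiority test, or that a participant without T1 is kept in it by any method.

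**The concern.** Three rules act together: no replacement of missing values, separate analysis of dropouts, and an ANOVA that needs both measurements. On their plain meaning, the superiority test runs on those who stayed. The plan therefore collects what an intention-to-treat analysis needs and then states a rule that does not use it.

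Dropping out happens after randomisation, and participants know their arm. The two arms also face different demands. The online arm follows sleep restriction, the one element from which the article expects adverse events. The waiting list gains access to the program after completing T1. The reasons for leaving may therefore differ by arm, and the remaining groups need no longer be comparable. The online versus waiting-list contrast carries the trial's causal claim, so its analysis set should not be left open to choice once the data are seen.

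**Working it through.** **1. The plan's own figures.** Inputs from the sample-size paragraph: α = .05, power .80, k = 3 groups, m = 2 measurements, r = .67, f = 0.38 or 0.25, dropout 50%.

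For the within-between interaction, λ = f²·N·m/(1 − r), df1 = (k − 1)(m − 1), df2 = (N − k)(m − 1).

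- f = 0.38, N = 15: λ = 0.1444 × 15 × 2/0.33 = 13.13, df 2 and 12, power 0.820.
- f = 0.25, N = 30: λ = 0.0625 × 30 × 2/0.33 = 11.36, df 2 and 27, power 0.821. (N = 29 gives 0.806; 30 makes the groups equal.)
- Dropout: 30/(1 − 0.50) = 60.

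All the stated sizes reproduce. The arithmetic is sound, and it shows that the trial is sized on the half expected to remain.

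**2. Who enters the superiority test.**

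| Participant | Dropouts analysed only separately | Separate analysis is an extra |
|---|---|---|
| Completes, T1 present | in | in |
| Drops out, T1 retrieved | out | in |
| T1 never obtained | out | out |

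The article does not choose between the columns. Under either one, everyone without T1 is deleted.

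**3. What selective loss could do (illustration).** Assumptions that are not in the document: zero true effect; the outcome is the T0 to T1 change; 20 per arm (60/3) or 30 per arm (60/2, if all 60 are in the online arms). The t-test on change is equivalent to the two-arm ANOVA interaction. From r = .67, SD of change = √(2(1 − .67)) = 0.81 baseline SD.

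*Closed form.* Let 50% of the online arm leave, with a dropout tendency correlated ρ with poor change, and let waiting-list dropout be unrelated to change. Then bias = ρ × 0.812 × φ(0)/0.5 = 0.648ρ. This gives 0.13, 0.19 and 0.32 SD at ρ = 0.2, 0.3 and 0.5. Simulated type I error at 20 per arm and 50% dropout in both arms is 7%, 8.5% and 13.5%, and about 20% at ρ = 0.5 with 30 per arm.

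*Simulation, logistic dropout.* The log-odds of leaving rise by 0.5 or 1.0 per SD of poorer change. Ranges run from slope 0.5 to slope 1.0.

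| Scenario | False benefit (SD) | Type I error |
|---|---|---|
| Dropout unrelated to change | 0 | about 5% |
| Online only selective, 50% vs 20%, 20 per arm | 0.19 to 0.33 | 9 to 17% |
| Same, 30 per arm | 0.19 to 0.34 | 11 to 23% |
| Same mechanism and 50% in both arms | about 0 | 4 to 6% |
| Same mechanism, 50% vs 20% | 0.11 to 0.20 | 6 to 12% |
| Online only selective, half of dropouts' T1 recovered at random and included | 0.06 to 0.12 | 5.5 to 7.5% |

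Repeat runs of the online-only scenarios reached 0.35 SD and 25%. For scale, the feasibility effect quoted in the article is d = 0.76.

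**4. Which remedy helps.** In the online-only scenario, a baseline-adjusted analysis of the same completers (close to a mixed model with only T0 and T1) still leaves 0.16 to 0.29 SD, against 0.19 to 0.34 for the ANOVA. That is 0.16/0.19 ≈ 84% of the bias. Including half of the missing T1 values removes well over half of it.

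**The case against.** The strongest defence is that no sentence confines the superiority test to completers. The separate analysis of dropouts could be an addition to an intention-to-treat analysis. A dropout who supplies T1 has both measurements, so repeated measures ANOVA would keep that person without imputation. Leaving the program is not the same as lacking T1, and the plan tries to recover T1. The 50% is a maximum taken from the feasibility study, and the Introduction says the platform and design were changed to reduce dropout. If the 60 spans three groups, some of the 60 are not randomised at all.

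Much of this stands. A reader might infer that the article declares a completer-only analysis which loses half of those randomised and inflates the program's effect. The document does not support that. Completer-only is an inference from three rules, half is a worst case, and the dropout mechanism is not given. Online participants who improve early might also stop, which would bias against the program. The same mechanism at the same rate in both arms gives no bias under no effect.

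The defence does not remove the point. The additional-analysis reading is not what the text says, and even under it everyone without T1 is deleted. Nor is this a detail that an article may leave to a fuller plan: the article states a rule, and on its plain meaning the rule conflicts with the stated aim.

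**Conclusion.** The point holds as a badly fixed rule. Read plainly, the analysis paragraph removes dropouts, at most 50% by the article's own figure, from the only randomised comparison. This includes those whose T1 has been obtained, and it conflicts with the purpose given for obtaining it. The validity argument concerns online versus waiting list only. The sample-size arithmetic is not in question.

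Bias arises if dropout relates to outcome differently in the two arms. Its size and direction cannot be derived from the document. The range of about 0.2 to 0.35 SD false benefit, with type I error of about 9 to 25%, rests on assumed outcome-related dropout in the online arm only and on zero true effect. It is not a forecast.

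**What to change.** 1. State that the primary online versus waiting-list analysis includes all randomised participants in their allocated arm, and that every T1 obtained after dropout enters that test. This matters most.
2. Replace the listwise ANOVA with a mixed model, or with multiple imputation by arm using T0 and the weekly diary data, so that participants still lacking T1 are retained.
3. Such methods correct little if dropout depends on the unseen outcome, so add a control-based or delta-adjusted sensitivity analysis for missing T1.
4. Keep the completer ANOVA and the separate description of dropouts, labelled as supportive.

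The cost is revised analysis wording and a little more analysis work; SPSS can fit the mixed model. Recruitment, treatment and planned data collection do not change. The estimate may become less favourable to the program.

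### For the randomised comparison on RIS, BDI-II and ESS, the planned repeated-measures ANOVA is valid but less precise than an ANCOVA adjusting T1 for T0, by about 11% in variance at 10 per arm

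*Protocol article*

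**What the plan says.** The data-analysis paragraph of the Methods names the method in one sentence, which covers the comparisons between groups as well: "superiority tests will be computed in SPSS using repeated measures ANOVA". No baseline covariate is mentioned there. The only adjustment foreseen elsewhere in the Methods is for changes in treatment or medication during the trial.

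The sample-size paragraph after Table 2 shows which effect is meant. The calculation was done "using the ANOVA repeated measures, within-between interaction setting of the G*Power software", with "the number of groups at 3, and the number of measurements at 2". It uses a feasibility effect that "was *d* = 0.76, corresponding to *f* = 0.38", and adds: "The correlation among the repeated measures reached a value of *r* = .67". The scale behind this correlation is not named. The plan then expects at least 30 evaluable participants, 10 per group, out of 60 allocated.

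Three design facts matter here:
- The two online groups are randomised 1:1 directly after the T0 scales are received.
- The face-to-face group is not randomised.
- BDI-II, RIS and ESS are taken at T0 and T1, whereas the first sleep diary opens only after allocation.

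**The concern.** With two time points, the group-by-time interaction compares mean change between groups, so T0 is treated as half of the outcome. In a randomised comparison a pre-allocation score can be a covariate instead. The analysis then estimates how strongly T1 depends on T0, where a change score fixes that slope at 1. When the correlation is well below 1, fixing the slope adds noise.

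What is at stake is precision. The randomised comparison may rest on about 10 people per arm, where power is limited and chance differences at T0 can be sizeable.

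**Working it through.** **Inputs.** From the sample-size paragraph: α = .05, power .80, k = 3 groups, m = 2 measurements, r = .67, f = 0.38 or 0.25, 10 evaluable per group. Assumptions added here: equal variances at T0 and T1 (set to 1), r = .67 for each of the three scales, a two-sided test, and a between-arm difference of 0.76 SD at T1. The last borrows the size of the feasibility d, which the article does not describe as a difference from a waiting list.

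**1. The plan's own figures.** The noncentrality is λ = f²·N·m/(1 − r), with k − 1 and N − k degrees of freedom.
- f = 0.38, N = 15: λ = 0.1444 × 15 × 2/0.33 = 13.13, power .820.
- f = 0.25, N = 30: λ = 0.0625 × 30 × 2/0.33 = 11.36, power .821.

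The next smaller balanced sizes fall short (N = 12: .683; N = 27: .771). So N = 15 and N = 30 both reproduce, which confirms that the trial is sized on the change-score test.

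**2. Large-sample variance, two randomised arms.**
- Change score: 2(1 − r) = 2 × 0.33 = 0.660.
- ANCOVA: 1 − r² = 1 − 0.4489 = 0.551.
- Ratio: (1 + r)/2 = 0.835, a reduction of 16.5%.

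**3. Correction for small arms.** Estimating the slope multiplies the ANCOVA variance by 1 + 1/(2n − 4), with n per arm.

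| n per arm | Factor | Ratio at r = .67 | Reduction |
|---|---|---|---|
| 10 | 1.0625 | 0.887 | 11% |
| 15 | 1.0385 | 0.867 | 13% |
| 20 | 1.0278 | 0.858 | 14% |

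Simulation (20,000 runs) gave ratios of about 0.88 at 10 per arm and 0.86 at 20 per arm. At 10 per arm the standard error is smaller by 1 − √0.887 = 6%, equivalent to 1/0.887 − 1 = 13% more participants.

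**4. Dependence on r at 10 per arm**, ratio = 1.0625 × (1 + r)/2.

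| r | Ratio | Reduction |
|---|---|---|
| .5 | 0.797 | 20% |
| .6 | 0.850 | 15% |
| .67 | 0.887 | 11% |
| .7 | 0.903 | 10% |
| .8 | 0.956 | 4% |
| .9 | 1.009 | none (1% larger) |

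**5. Power for 0.76 SD at r = .67**, including the slope penalty and the lost degree of freedom.

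| n per arm | Change score | ANCOVA |
|---|---|---|
| 10 | .51 | .56 |
| 15 | .70 | .76 |
| 17 | .75 | .81 |
| 19 | .80 | .86 |

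With 16 per arm ANCOVA reaches .79, so 80% power needs 17 per arm against 19, or 34 against 38 evaluable.

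**6. Chance imbalance.** With 10 per arm the standard error of the T0 difference is √(2/10) = 0.45 SD. Given an imbalance of that size, the change-score estimate shifts by (1 − r) × 0.45 = 0.15 SD. This is already counted in step 2: 0.660 = 0.551 + (1 − r)² = 0.551 + 0.109. It is the source of the precision loss, not an additional harm.

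**The case against.** The strongest reply is that nothing in the plan is wrong. The named test and the sample size agree, the planned N reproduces, and the simulated type I error of the change-score test at 10 per arm is .051. Over repeated randomisation its estimate is unbiased. All of this stands. A reader might infer that the analysis is invalid or biased by baseline imbalance. The documents do not support that, because allocation is random and imbalance averages to zero.

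A second reply is that covariates may be set out in a fuller document. That is possible, but the article does name the test, and its sample size treats T0 as a repeated outcome. The point is therefore about the method chosen, not about missing detail.

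A third reply is that the 16.5% figure does not apply to a trial of this size, that ANCOVA is not better in every case, and that the change is not free. This also stands. At 10 per arm the reduction is about 11%, near r = .9 it disappears, and one error degree of freedom is spent.

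A fourth reply concerns scope, and it is correct. For the face-to-face group, ANCOVA and change scores can estimate different things: with a baseline difference of 0.5 SD they differ by 0.33 × 0.5 = 0.165 SD. The choice there is an assumption about confounding, on which the Discussion itself urges caution. Sleep efficiency has no value before allocation, so the argument does not reach it.

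**Conclusion.** The point holds as an avoidable inefficiency in the randomised comparison on RIS, BDI-II and ESS, and not as an error or contradiction. At the plan's r = .67 the variance reduction is about 11% at 10 evaluable per arm. Under the assumed 0.76 SD difference this is worth about 5 percentage points of power at 10 per arm, 6 at 15 per arm, and about two participants per arm at 80% power.

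The size rests on a single correlation for an unnamed scale, equal variances at the two times, and a between-arm effect that the article does not give. It will differ between the three scales. It is worth acting on because the trial is small and T0 is already collected.

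**What to change.** In the data-analysis paragraph of the Methods, state that for RIS, BDI-II and ESS the primary test of online versus waiting list is an ANCOVA of the T1 score with arm and T0 score, in the randomised arms only, with the adjusted difference reported with its 95% CI. Keep repeated-measures ANOVA as a supportive analysis. Set out comparisons with the face-to-face group and the analysis of sleep efficiency separately, since this argument does not cover them.

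The cost is one error degree of freedom and one line of SPSS syntax, with no extra participants or data. The change should be recorded before outcomes are analysed by arm.
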